**
[figure not shown]
**

**11. APPENDIX 1 …………………………………………………………………………………… 10**

| **BACKGROUND AND RATIONALE** |  |
| --- | --- |
| Healthcare systems around the world are struggling to meet the increasing demand for hospital resources. Ageing populations and the increasing prevalence of chronic diseases and co-morbidities exacerbate this rising demand [1]. Singapore’s population is one of the most rapidly ageing in Asia with an increasing chronic disease burden [2, 3]. Care is fragmented and episodic and the lack of integration between the well-developed tertiary hospitals and less-developed primary and community care sectors is well acknowledged. There are concerns over the long term sustainability of a hospital centric care model; therefore there has been great interest to develop integrated care programs that provide more cost-effective care to high risk patients with multi-comorbidities and reducing the dependence on hospital resources.  The Virtual Ward model was first developed in Croydon, United Kingdom. While there are anecdotal reports of its effectiveness, the program has not been formally evaluated. Our hospital performed a randomized controlled trial using the virtual ward care model for high risk patients with a LACE score of 10 or more [4] in 2011, but did not find a significant reduction in readmissions and emergency department [ED] visits. It is possible that the virtual model of care is simply too weak an intervention to reduce readmissions for high risk patients with complex care needs. Emerging evidence also suggest interventions may be more effective when they are started early in the admission [5] and in the form of multi-component bundles [5, 6] instead of single interventions.  While there is face validity to these conceptual frameworks, delivering pre and post-discharge care in a coordinated manner has practical challenges in operations and logistics. The lack of horizontal integration between healthcare providers is well acknowledged as an impediment to achieving good outcomes in care integration initiatives. Integrated Practice Units (IPUs) have been proposed by Michael Porter as a way to organize healthcare teams [7]. With buy-in from the hospital management and relevant stakeholders, we propose to utilize the IPU concept to organize our inpatient clinical team and outpatient virtual ward team to deliver pre-discharge and post-discharge interventions in a coordinated manner in the Singapore General Hospital. The IPU would be led by a senior family physician, physically co-located, share a similar administration structure under an Office of Integrated Care, a common patient clinical record and be responsible for shared process and outcome indicators.  In this study, our objective is to study the effectiveness of an IPU in providing holistic care which starts during inpatient admission and continue this with seamless outpatient support from our virtual ward intervention. The primary outcome of interest would be the 30-day readmission rate.  References:  1. 1. National Institute on Aging, National Institutes of Health, U.S. Department of Health and Human Services. Global health and ageing report: The World Health Organization; 2011. Available from: http://www.who.int/ageing/publications/global_health.pdf.  2. Khalik S: Bed Crunch Time Again at Some Public Hospitals. The Straits Time [Singapore] 2011. http://www.healthxchange.com.sg/News/Pages/Bed-crunchtime- again-at-some-public-hospitals.aspx.  3. Khalik S: Public Hospital ‘borrowing’ Ward Space. The Straits Time [Singapore]  4. van Walraven C, Dhalla IA, Bell C, Etchells E, Stiell IG, Zarnke K, Austin PC, Forster AJ. Derivation and validation of an index to predict early death or unplanned readmission after discharge from hospital to the community. *CMAJ* 2010, 182(6):551-557.  5. Hansen LO, Young RS, Hinami K, Leung A, Williams MV. Interventions to Reduce 30-Day Rehospitalization: A Systematic Review. Ann Intern Med. 2011;155(8):520-8.  6. Jack BW, Chetty VK, Anthony D, Greenwald JL, Sanchez GM, Johnson AE et al. A reengineered hospital discharge program to decrease rehospitalization: a randomized trial. Ann Intern Med. 2009;150(3):178-87.  7. Porter ME, Teisberg EO. Redefining health care: Creating value-based competition on results. Boston, Massachusetts: Harvard Business School Press; 2006. |  |
| **HYPOTHESIS AND OBJECTIVES** |  |
| The main aim of our study is to find out if our integrated care model can reduce the rate of unscheduled readmission and emergency department visits of high risk patients in the Singapore General Hospital.  Based on our previous study, we hypothesize that our intervention could reduce 30-day readmission rate by approximately 25% for patients enrolled in the intervention group in order to be clinically significant.  Other secondary outcomes include:   1. Unplanned readmission rate to any hospital within 90 days, 180 days of discharge, 2. Emergency department (ED) attendance rate within 30 days, 90 days, 180 days of discharge 3. Probability without readmission or death up to 180 days 4. Index admission and post-discharge mortality rate at 90-day 5. Cumulative length of hospital stay at 90 days 6. Number of outpatient specialist clinic visits at 90-day and 180-day |  |
| **EXPECTED RISKS AND BENEFITS** |  |
| There is no higher than expected risk to study participants. |  |
| **STUDY POPULATION** |  |
| List the number and nature of subjects to be enrolled. |  |
| Patients who are eligible for the study would be all adults patients admitted to participating medical wards (general internal medicine, endocrinology, respiratory medicine, renal medicine, gastroenterology, neurology) in Singapore General Hospital, who has a LACE score of ≥10 and 1 or more unscheduled admission in the past 90 days.  Based on our sample size calculation, we will need to randomize a total of 840 patients in a 1:1 ratio to the intervention and control groups. |  |
| Criteria for Recruitment and Recruitment Process |  |
| The research coordinator will first enquire if the subjects are interested and willing to participate in the study. For eligible and consented patients, the research coordinator will obtain their written consent and proceed with the randomization process. |  |
| Inclusion Criteria |  |
| - Ability to speak English and/or Mandarin. - Singaporeans/ Singapore Permanent Residents. - Aged 21 years and above - LACE score >=10 |  |

| Our study design is an open label, outcome assessor blinded randomised controlled trial.  Randomisation: 840 patients will be randomized in a 1:1 ratio using blocks of 6 into the intervention and control groups. Randomisation sequence will be generated by computer software. Allocation concealment is effected via an off-site telephone service maintained by a hospital administrator.  On every working day, the study team members will receive a list of patients who has been readmitted in the past 90 days. The study team members will then screen through the list for eligibility criteria and their LACE scores. For suitable patients, they will be approached and recruited by the research coordinator at the bedside during their hospitalisation. After consent, randomisation will be carried out. Patients allocated to the intervention group are intervened for 90 days and patients allocated to the control group will receive usual care.  Intervention:  The intervention can be divided into 2 parts. Inpatient and outpatient intervention (Appendix 1). The study team is also divided into the 2 teams. Inpatient and outpatient virtual ward (VW) team. The inpatient team is led by an attending family physician, a junior doctor, a nurse case manager, and a part-time (0.1 Full Time Equivalent) pharmacist while the outpatient VW team comprised of an attending family physician and two nurse case managers. A medical social worker who spends 0.5 full time equivalent time in the team supports both the inpatient and outpatient teams.  Inpatient intervention starts when the patient assigned to the intervention is medically stable to be transferred over to the inpatient clinical team. The inpatient team will continue to optimize the patient’s medical conditions and also systematically identify preventable reasons for readmission. Medications will be reconciled with input from the pharmacist and the appropriate community and social services necessary to support the patient’s transition to home will be activated.  Another core component is patient education and coaching. The nurse case managers will use standardized action plans for chronic diseases (examples include congestive cardiac failure, diabetes mellitus, asthma, chronic obstructive pulmonary disease, chronic kidney disease) for patient education. Finally, an individualized care plan complete with written discharge instructions, patients’ appointments, medication changes and the contact information of the outpatient nurse case manager is to be provided to all patients on discharge. The patient’s care is then handed over to the outpatient virtual ward team at the bedside for a seamless information transfer.  At the home setting, the outpatient nurse case manager will follow up with a telephone call within 72 hours of discharge to assess the patient’s condition and ensure adherence to the prescribed care plans and successful activation of community services. This is followed by a home assessment within one week of discharge. During the home assessment, the nurse case manager will assess the patient’s medical condition and health literacy, competency of the care-giver, availability of nursing and home care equipment, adequacy of social support, safety of the home environment and adherence to medication. Each nurse will be in charge of an average of 30 patients at any time during the program.  A multidisciplinary team meeting will be conducted in the morning of every working day. New patients will be discussed and their care plans reviewed. During the meeting, each nurse case manager is to report on the status of patients under her care. Patients who develop urgent deterioration of their chronic conditions and new medical issues will be recalled to the early review clinic to be reviewed by the family physician. Patients who are doing well in the intervention can be reviewed less frequently at the team meetings. Throughout the intervention period, the nurse case managers are contactable during office hours. Scheduled calls to check in on the patients will be made about once a week. Our intervention will last for 90 days after discharge and patients will be discharged at the end of the intervention period to a primary care provider in the community with continuing specialist input as warranted.  Control Group:  Patients in the control group will receive usual medical care provided by the admitting inpatient team of the hospital. On discharge, patients can be referred to primary care provider, specialists in the outpatient clinic and ambulatory community services as considered necessary by the medical team. As part of standard hospital care, patients will receive an abbreviated standardized patient copy of the hospital discharge summary listing their medical diagnoses and medications. For this study, there will be no contact between patients in the control group and the study team throughout the 3-month interval. A scheduled telephone call will be made at the end of the 3-month study period to verify patient outcomes.  Outcomes:  All outcomes are objectively extracted from the hospital electronic health records and the National Electronic Health Records by an assessor blinded to the treatment allocation.  The primary outcome measure is the 30-day unplanned readmission rate.  Other secondary outcomes included:   1. Unplanned readmission rate to any hospital within 90 days, 180 days of discharge, 2. Emergency department (ED) attendance rate within 30 days, 90 days, 180 days of discharge 3. Probability without readmission or death up to 180 days 4. Index admission and post-discharge mortality rate at 90-day 5. Cumulative length of hospital stay at 90 days 6. Number of outpatient specialist clinic visits at 90-day and 180-day |  |
| **DATA ANALYSIS** |  |
| Data Entry and Storage |  |
| Data entry is made by a trained research co-ordinator into Redcap (Research Electronic Data Capture), a free secure, web-based application designed to support data capture for research studies. Data will be stored in Redcap. Only investigators with access to Redcap can access the data.  **6.2 Data Quality Assurance**  Outcome information will be obtained from the hospital electronic health records and the National Electronic Health Records. Phone follow up will be at 90 days to verify the outcomes information. Information will also be downloaded from routinely used critical care monitors, defibrillators and event records. Public accessible death certificate information will also be reviewed.  Additional steps to ensure data quality includes use of standardized forms, uniform criteria for patient recruitment, internal monitoring of data collection, range checks and verification built into the data entry system and a sequence of logic checking and examination of variables. |  |
| **SAMPLE SIZE AND STATISTICAL METHODS** |  |
| Determination of Sample Size |  |
| We hypothesize that our intervention could reduce readmissions by approximately 25% for patients enrolled in the intervention group. We estimate the baseline readmission rate of eligible patients to be 40% within 30 days of discharge. Based on a power of 80%, level of significance at 5%, and attrition at 10%, a sample size of 420 in each group is required. All statistical analysis will be performed on an intention-to-treat basis. |  |
| **7.2 Statistical and Analytical Plan**  The baseline characteristics will be presented as mean ± SD for continuous variables and frequency counts and percentages for categorical variables. For baseline variables, the 2-sample t-test will be used to compare means and the Pearson chi-square test to compare proportions. A Poisson regression model will be used to obtain relative risks of readmission and ED visits. Kaplan-Meier method will be used to study the survival distribution (based on time to readmission or death) of the intervention and control groups. All tests of significance used 95% level (p<0.05). No subgroup analysis was planned in this study. |  |
| **DIRECT ACCESS TO SOURCE DATA/DOCUMENTS** The investigator(s)/institution(s) will permit study-related monitoring, audits and/or IRB review and regulatory inspection(s), providing direct access to source data/document.   **ETHICAL CONSIDERATIONS** This study will be conducted in accordance with the ethical principles that have their origin in the Declaration of Helsinki and that are consistent with the Singapore Good Clinical Practice and the applicable regulatory requirements.  This final study protocol, including the final version of the Participant Information and Informed Consent Form, must be approved in writing by the Centralised Institutional Review Board (CIRB), prior to enrolment of any participant into the study.  The principle investigator is responsible for informing the CIRB of any amendments to the protocol or other study-related documents, as per local requirement. |  |
| Informed ConsentConsent will be taken by the research co-ordinators after explaining the study protocol, obtaining voluntary agreement of the participant, explaining the number of visits and alternatives and after the participant is clear of his/her study rights. |  |
|  |  |
| Confidentiality of Data and Participant Records |  |
| Research data and participant database will be stored in Redcap (Research Electronic Data Capture), a free secure, web-based application designed to support data capture for research studies. Data will be stored in Redcap. Only investigators with access to Redcap can access the data.  Once data entry is completed, all identifiers will be subsequently removed from the dataset. No further follow up (more than 90 days) is required. No coded research data will be disseminated to any third parties not involved in the research study. All patient identifiers will be removed from the database to protect patient confidentiality. |  |
| **FUNDING** | |
| This is an investigator-initiated study, and supported by a project grant from the Agency of Integrated Care Singapore (AIC/RPD/RD-OIC/ICCS/010/05-2011). | |

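### The protocol plans significance tests of baseline variables between randomised arms and names no covariate for the readmission model, although the screening LACE score is available for a free, possibly small, gain in precision

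*Protocol*

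**What the plan says.** Section 7.2 of the protocol (Statistical and Analytical Plan) first plans a descriptive baseline table: means with standard deviations, counts and percentages. It then adds tests between the arms: "For baseline variables, the 2-sample t-test will be used to compare means and the Pearson chi-square test to compare proportions". For the outcome it says: "A Poisson regression model will be used to obtain relative risks of readmission and ED visits". No covariate is listed, and the model is called neither adjusted nor unadjusted.

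The methodology section describes allocation as follows: "840 patients will be randomized in a 1:1 ratio using blocks of 6 into the intervention and control groups". The sequence is computer-generated and concealed by an off-site telephone service, and no stratification factor is named. On screening, which comes before consent and randomisation, it says: "The study team members will then screen through the list for eligibility criteria and their LACE scores". The reference cited for LACE under Background and Rationale describes it as an index for predicting early death or unplanned readmission after discharge. That is close to the primary endpoint: "The primary outcome measure is the 30-day unplanned readmission rate".

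**The concern.** There are two linked points.

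- **Baseline tests.** A test of baseline balance asks whether chance produced the difference. Under sound randomisation that is already known. Some small p-values will still appear, and they have no clear use. If covariates are not fixed in advance, they leave room for an adjustment set chosen after the baseline data are seen.
- **Unused covariate.** The trial selects patients on a score meant to predict readmission and reads it before randomisation, but section 7.2 gives it no role in the readmission model. Adjusting for a prognostic baseline covariate usually narrows the confidence interval without adding patients.

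At stake are a modest amount of precision and clear pre-specification. The validity of the primary comparison is not in question.

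**Working it through.** **Inputs from the protocol.** Control rate: "We estimate the baseline readmission rate of eligible patients to be 40% within 30 days of discharge". Effect: "We hypothesize that our intervention could reduce readmissions by approximately 25% for patients enrolled in the intervention group", read as relative, so 40% v 30% and RR 0.75. Size: "Based on a power of 80%, level of significance at 5%, and attrition at 10%, a sample size of 420 in each group is required". Sidedness is not stated; two-sided is assumed.

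**Step 1: reproduce 420 per arm.** Two proportions, two-sided 5%, 80% power:

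n = [1.96·√(2·0.35·0.65) + 0.8416·√(0.4·0.6 + 0.3·0.7)]² / 0.10² = 356.

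With continuity correction: (356/4)·[1 + √(1 + 4/(356·0.10))]² = 376. Allowing for 10% attrition: 376/0.9 = 418, which agrees with 420.

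**Step 2: power without adjustment.** Analysed per arm: 420 × 0.9 = 378.

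- Two proportions: 82.3%.
- Log relative risk with robust variance: SE = √[0.6/(378·0.4) + 0.7/(378·0.3)] = 0.1007. Then |ln 0.75|/0.1007 = 2.857, and Φ(2.857 − 1.96) = 81.5%.

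The planned size therefore does not rely on adjustment.

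**Step 3: what adjustment could add.** If baseline covariates explain a share R² of the outcome variance, the variance of the log relative risk falls by roughly the factor (1 − R²), and effective n is 378/(1 − R²). The protocol gives no R² or c-statistic, so these values are assumptions.

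| Assumed R² | CI width v unadjusted | Equivalent n per arm | Power |
| --- | --- | --- | --- |
| 0 | 100% | 378 | 81.5% |
| 0.02 | 99% | 386 | 82.3% |
| 0.05 | 97.5% | 398 | 83.4% |
| 0.10 | 95% | 420 | 85.3% |

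**Step 4: simulation with a truncated score.** Eligibility requires LACE of 10 or more, which narrows its range. A LACE-like score running from 10 to 19, at 378 per arm and 40% v 30%, was analysed by robust-variance Poisson regression with and without the score.

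| Assumed c-statistic | More effective patients | Of 756 analysed |
| --- | --- | --- |
| 0.50 | 0% | 0 |
| 0.56 | about 1% | about 8 |
| 0.60 | about 3% | about 23 |
| 0.64 | about 6% | about 45 |
| 0.685 | about 11% | about 83 |

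The last column is the percentage times 756. This agrees with step 3, where R² = 0.10 gives 420/378 = 1.11.

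**Step 5: the gain depends on the variance estimator.** In a separate simulation with LACE and prior admissions as covariates (R² 0.056, c = 0.63), adjustment raised power from 81.1% to 83.9% with robust errors. With model-based Poisson errors it moved only from 67% to 68%.

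**Step 6: the baseline tests.** With k independent baseline variables tested at 5%, the chance of at least one p<0.05 is 1 − 0.95^k. The number of variables is not stated. For an assumed 10 to 20, this is 40% to 64%, even when allocation worked perfectly.

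**The case against.** **A reader might infer that the primary analysis is unadjusted.** The protocol does not say so. It names no covariate but excludes none, and a covariate list is often left to a statistical analysis plan, which is not shown here. This objection stands, and silence alone is no error. What remains is that the protocol commits in writing to the baseline tests, and that a better use of baseline data is at hand.

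**A reader might infer that the trial is biased or underpowered.** It is neither on this ground. A randomised unadjusted comparison is unbiased, its standard error already allows for chance imbalance, and step 2 shows over 80% power. Permuted blocks without strata are an acceptable design for 840 patients.

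**The gain may be close to nothing.** This also stands. Truncation at LACE 10 limits prognostic range, and no strength is documented. Against that, adjusting for a useless score cost nothing in the simulation.

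**Prior-admission history may not be usable.** The screening list shows that a recent admission occurred, but recording of a count is not stated. The Study Population text requires at least one unscheduled admission in 90 days, while the bulleted inclusion list omits it. Only LACE can be treated as available for every patient.

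**Post hoc covariate selection is speculative.** Section 7.2 does not link the baseline tests to the model. It is a risk that pre-specification removes, and the protocol does not plan it.

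**Conclusion.** The point holds as a no-cost improvement. The baseline tests are stated plainly and serve no purpose in a randomised comparison. A pre-randomisation score that the protocol itself presents as predictive is given no stated place in the readmission model. Including it would be worth about 0% to 11% more effective patients. That range rests on assumed c-statistics of 0.50 to about 0.68, a relative risk of 0.75 from a 40% control rate, 378 analysed per arm and robust variance. The lower end is quite possible. The documents do not support calling the current plan invalid or underpowered.

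**What to change.** - Keep the descriptive baseline table by arm and delete the baseline t-tests and chi-square tests.
- Define the primary model as a Poisson regression with robust variance on arm and screening LACE score (continuous). Add the number of unscheduled admissions in the previous 90 days if that count is recorded for every patient before randomisation.
- Report the unadjusted relative risk as a supportive result.
- State that the covariates are fixed in advance and will not be chosen from baseline p-values.

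The cost is a few sentences in section 7.2, or in the statistical analysis plan, before outcome data are examined. LACE needs no new data collection because it is already read at screening. For the admission count, the team should first confirm that it is captured. Sample size and trial conduct do not change.

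### Protocol 7.2 names a Poisson model for a primary outcome sized as a proportion and states no robust variance; with the model's default variance, power would be about 67–73% instead of 80%

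*Protocol*

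**What the plan says.** Under Study Design, Outcomes, the Protocol states: "The primary outcome measure is the 30-day unplanned readmission rate". It does not say in words whether this is any versus none per patient or a count of readmissions.

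Determination of Sample Size treats it as a proportion of patients. The control figure is given as "We estimate the baseline readmission rate of eligible patients to be 40% within 30 days of discharge", the effect as "We hypothesize that our intervention could reduce readmissions by approximately 25% for patients enrolled in the intervention group", and the result as "Based on a power of 80%, level of significance at 5%, and attrition at 10%, a sample size of 420 in each group is required".

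Section 7.2 gives one sentence on the model: "A Poisson regression model will be used to obtain relative risks of readmission and ED visits". This is the only model named for readmission. The chi-square test in the same section is assigned to baseline variables, and the Kaplan-Meier method to time to readmission or death. The sentence on the Poisson model does not say whether its standard errors are model-based or robust.

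**The concern.** The sample size and the named model rest on different variance assumptions for the same outcome. A two-proportion calculation uses the binomial variance p(1−p). A Poisson likelihood uses variance p, which is larger by a factor 1/(1−p). For a rare event the difference is negligible. At readmission risks of 30–40% it is not.

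Poisson regression still estimates the relative risk correctly for a yes/no outcome. What goes wrong is the standard error taken from the Poisson likelihood, and with it the p-value and the confidence interval, which become too wide. This is the reverse of the over-dispersion expected in repeat-event counts such as ED visits.

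At stake is the power of the primary comparison. A real reduction of the planned size could be reported as non-significant because of a software default. Because 7.2 leaves the choice open, two analyses that both fit its wording could also reach different conclusions from the same data.

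**Working it through.** **Inputs.** From Determination of Sample Size: control risk 40%; reduction 25%; power 80%; significance 5%; attrition 10%; 420 per arm. From Study Design: 1:1 allocation, 840 in total. The 25% is read as relative (40% to 30%, relative risk 0.75), because an absolute drop of 25 points would need only about 49 per arm. Sidedness is not stated; two-sided is used because one-sided versions give only 313 to 334 per arm after attrition.

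**Step 1: reproduce 420.** Two-proportion formula, 0.40 versus 0.30, two-sided 5%, 80% power:
- without continuity correction: 356 per arm; 356/0.9 = 396
- with continuity correction: 376 per arm; 376/0.9 = 418, which is about 420

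So the stated figure is a comparison of two proportions. After 10% attrition, 420 × 0.9 = 378 per arm are analysed.

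**Step 2: the two standard errors of the log relative risk, n = 378 per arm.**
- Poisson model-based: √(1/(n·0.4) + 1/(n·0.3)) = √(1/151.2 + 1/113.4) = 0.1242
- Binomial (true for a yes/no outcome): √(0.6/(n·0.4) + 0.7/(n·0.3)) = √(0.6/151.2 + 0.7/113.4) = 0.1007
- Ratio: 0.1242/0.1007 = 1.23
- Under the null with 40% in both arms the ratio is 1/√(1−0.4) = 1.29

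**Step 3: power.** The log relative risk to detect is |ln 0.75| = 0.2877. The test rejects when the estimate exceeds 1.96 model standard errors, while the estimate itself varies with the binomial standard error:

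power = Φ((0.2877 − 1.96 × SE used)/SE true)

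- Model-based, n = 378: (0.2877 − 1.96 × 0.1242)/0.1007 = 0.44, power 67.0%
- Robust, n = 378: (0.2877 − 1.96 × 0.1007)/0.1007 = 0.90, power 81.5%

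The same formula and a simulation of 400,000 trials per setting give:

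| Analysed per arm | Model-based: formula / simulated | Robust: formula / simulated |
|---|---|---|
| 378 | 67.0% / 67.3% | 81.5% / 82.2% |
| 420 (no attrition) | 72.4% / 72.7% | 85.3% / 85.8% |

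An exact binomial calculation agrees: 67.3% and 82.3% at 378 per arm, 72.8% and 85.9% at 420.

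**Step 4: type I error.** With 40% in both arms, the model-based test rejects only when the estimate exceeds 1.96 × 1.29 = 2.53 true standard errors, so the actual two-sided level is about 1.1%. Simulation gives 1.1% with the model-based and 5.0% with the robust variance (exact calculation at 378: 1.1% and 4.9%).

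**Step 5: cost of keeping the default variance.** By the Step 3 formula, about 490 analysed per arm would be needed for 80% power. There the model-based standard error is 0.1091 and the true one 0.0884, so (0.2877 − 1.96 × 0.1091)/0.0884 = 0.83, power 79.8%. That is 490 − 378 = 112 more per arm than planned.

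**The case against.** The strongest reply is that 7.2 does not specify the default variance. It names a Poisson model and is silent on the standard error. Poisson regression aimed at relative risks is a common way to describe the robust-variance method, and under that reading the stated 80% is met. The option for the standard error is also a detail that a statistical analysis plan often settles, and that plan is not shown here. This stands as far as it goes. A reader might infer that the trial's power simply is 67% and that its primary test runs at 1%. The Protocol does not support that: both figures hold only if the model-based variance is used.

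Three further points are fair:
- Any versus none per patient is inferred from the 40% baseline, the two-proportion sample size and the term relative risk. It is not written down. The same sentence in 7.2 also covers ED visits, which may be counts.
- The 10% attrition is a planning allowance. With intention-to-treat analysis and outcomes taken from hospital and national records, nearly all 420 per arm might be analysed, and the conditional power is then about 73%.
- The error is conservative. The relative risk is not biased and false positives fall.

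These points lower the severity but do not remove the issue. The Protocol itself chose the model for a common outcome and claimed 80% power, and the two agree only with a variance that it does not state. The standard likelihood variance of the named model misses 80% even with no attrition.

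**Conclusion.** The point holds conditionally. Protocol 7.2 names a Poisson model, without a robust variance, for an outcome that the sample size treats as a proportion. If the model's own variance is used, confidence intervals for the log relative risk are about 23% too wide at the planned risks (29% under the null at 40%). Power is then 67% with 378 analysed per arm and 73% with 420, against 82% and 86% with a robust variance.

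This rests on readmission being any versus none per patient, risks of 40% and 30%, and a two-sided 5% test. It is a should-fix item: it could cost the trial a true finding, but it does not bias the estimate or raise the false-positive rate.

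**What to change.** In 7.2, add that readmission within 30, 90 and 180 days is analysed as any versus none per patient, by Poisson regression with a robust (sandwich) variance or by a log-binomial model, and that the primary p-value and 95% confidence interval come from that analysis. If a statistical analysis plan exists, give it the same wording. Settle this before outcomes are examined by arm, because the choice can decide significance.

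The cost is one sentence and one software option. No extra patients or data are needed, the relative risk stays the effect measure, and with the robust Poisson model its estimate does not change. The planned 420 per arm then delivers the stated power.
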